**Discussion:**

This RCT aims to clarify whether the WNJT can result in reduced incidences of hypoxemia and complications and provide improved satisfaction to the anesthetist, physician, and patient. Thus, it can be determined if the WNJT is a useful tool for supplement oxygen in obese patients undergoing gastroscopy with intravenous propofol anesthesia. The results will provide the evidence for anesthesiologists to make a decision regarding the choice of supplementary oxygen methods in this condition.

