#### Data after the procedure

Satisfaction of the anesthetist, physician, and patient is assessed using a 10-point visual analog scale at the time of patient’s consciousness recovery and 30 min after consciousness recovery, respectively, and classed as follows: poor, 1–4; fair, 5–7; and good, 8–10 [25]. Adverse events such as sore throat, nasal bleeding, nausea, and vomiting are also collected at the time when the patient recovers consciousness and 30 min after the recovery of consciousness.

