#### Secondary outcomes

The secondary outcomes are the adverse events during the gastroscopy, nasal bleeding or injury, complications, and satisfaction of the anesthetist, physician, and patient.

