### Sample size estimation and statistical analysis

The sample size is calculated with the Pass software (version 11.0, NCSS, LLC, Kaysville, UT, USA). The two independent proportions procedure is used. With an α = 0.05 and a power of 80%, we estimated that 140 patients per group would be required for our study. If the dropout rate is set at about 10%, a total of 308 patients (154 in each group) would be required. The incidence of hypoxemia during gastroscopy in obese patients with intravenous propofol anesthesia has been reported to be 22% [20]. Thus, a proportion of 22% of the patients in the group B is expected to develop hypoxemia. P1 and P2 are calculated from the assumption that the WNJT would achieve a reduction from 22% to 11% for the incidence of hypoxemia.

Statistical analysis of data will be performed using the SPSS (Version 23.0, SPSS Inc., Chicago, IL, USA) by a blinded statistician. Continuous variables will be presented as mean ± standard deviation (normally distributed data) or medians and ranges (non-normally distributed data). Numerical data will be compared using a Student’s t-test (normally distributed data) or Mann–Whitney rank sum test (non-normally distributed data). Qualitative data will be expressed as n (%) and compared using a Chi-squared test. A *P* value < 0.05 is considered statistically significant.

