## Discussion

Hypoxemia caused by transient respiratory inhibition and airway obstruction is common during gastroscopy with intravenous anesthesia or sedation, especially in obese patients due to altered anatomy of the airway, reduced functional residual volume of the lungs, and decreased compliance of the chest wall [12]. Although respiratory depression may be transient and spontaneously recover with or without intervention, it can result in a risk of interrupting or stopping the gastroscopic procedure and even lethal hypoxemia requiring emergent management. The nasopharyngeal airway can prevent airway obstruction caused by the falling tongue and reduce air flow resistance, thus facilitating spontaneous breathing and decreasing the occurrence of hypoxemia during gastroscopy with intravenous anesthesia or sedation [26].

This RCT is designed to test the hypothesis that the WNJT, a new kind of nasopharyngeal airway, can reduce the incidence of hypoxemia and related adverse events. We believe that the findings of this study will have significant clinical implications; even negative results are obtained. This would mean that more studies are needed to explore a safe and effective method to prevent hypoxemia during gastroscopy with intravenous anesthesia or sedation in obese patients. This is one of the main strengths of present study.

There are some issues in our study design that need to be noted. First, this is a single-blinded protocol, as the investigator knows whether nasal prongs or the WNJT are used. This may bias the findings of this study. Second, as the nasal soft tissue is easily damaged [27], the WNJT may lead to discomfort and even nasal bleeding or injury, as reported in a previous study [15]. Furthermore, the nasal bleeding or injury may only occur in the group A. Although the nasal bleeding and injury associated with nasopharyngeal airway are often slight, care should be taken to avoid this; essential management is required if they occur, especially for patients with nasal stenosis [28].

In summary, this single-center, prospective RCT will compare the efficacy and safety of using the WNJT and nasal prongs for supplemental oxygen during gastroscopy with intravenous propofol anesthesia in obese patients. The result of the trial will provide the evidence for anesthesiologists to make a decision regarding the choice of supplemental oxygen methods in this condition.

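### One unrestricted P < 0.05 rule covers the primary outcome and roughly 18 to 21 secondary comparisons, although the stated aim includes fewer complications and better satisfaction

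*Protocol article*

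**What the plan says.** All references are to the protocol article.

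- **Sample size estimation and statistical analysis.** The section assigns tests by type of data (t-test or Mann–Whitney for numerical data; for categories, "Qualitative data will be expressed as n (%) and compared using a Chi-squared test"). It then states that a P "value < 0.05 is considered statistically significant". Neither the choice of test nor the threshold distinguishes primary from secondary outcomes.
- **Secondary outcomes.** "The secondary outcomes are the adverse events during the gastroscopy, nasal bleeding or injury, complications, and satisfaction of the anesthetist, physician, and patient".
- **Data about the procedure** and **Data after the procedure.** These sections list the individual events. Post-procedure events are collected on waking and 30 minutes later. Satisfaction is scored "at the time of patient’s consciousness recovery and 30 min after consciousness recovery, respectively", which leaves open whether each rater scores once or twice.
- **Abstract, Discussion paragraph.** The aim is to clarify whether the WNJT "can result in reduced incidences of hypoxemia and complications and provide improved satisfaction to the anesthetist, physician, and patient".
- **Discussion.** The hypothesis is narrower: that the device "can reduce the incidence of hypoxemia and related adverse events".

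**The concern.** The sample size is built on hypoxemia alone, yet the abstract's aim also covers complications and the satisfaction of three people. The only rule for calling any of these results significant is the same 5% threshold, applied one comparison at a time. Nothing says which rater, time point or event carries the complication or satisfaction part of the aim, or that these results are only supportive.

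With many comparisons, some will pass 5% by chance. An isolated result, such as less cough or a higher score from one rater, would meet the written rule and fit the written aim. Those parts of the conclusion would then rest on tests without control of the overall error.

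**Working it through.** **Plan's own figures.** The article gives no family-wise error figure to reproduce. Its one design calculation concerns the primary outcome: "With an α = 0.05 and a power of 80" per cent, assuming that "the WNJT would achieve a reduction from 22% to 11% for the incidence of hypoxemia". The formula is

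n = [z_α √(2p̄q̄) + z_β √(p₁q₁ + p₂q₂)]² / (p₁ − p₂)², with p̄ = 0.165 and q̄ = 0.835.

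- One-sided α: (1.645 × 0.525 + 0.842 × 0.519)² / 0.0121 = 139.7, so 140 per group, as stated.
- Two-sided α: 177.6, so 178 per group.

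That gap is a separate matter. It is noted here only because the article does not state sidedness. Below, each test is taken as two-sided, as a chi-squared test is by default: 5% false positives in total and 2.5% in each direction.

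**Step 1: count the secondary comparisons** (my count; the article gives none).

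- During endoscopy: body movement, vomiting, regurgitation/aspiration, bronchospasm, cough, bradycardia, tachycardia, hypertension, hypotension = 9.
- Afterwards: sore throat, nausea and vomiting, each at two time points = 6.
- Satisfaction: three raters = 3, or 6 if each scores at both times.
- Total: 9 + 6 + 3 = 18, or 9 + 6 + 6 = 21.

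Nasal bleeding is left out: the Discussion expects it only in the WNJT group, so it cannot produce a false benefit. A different tally (one time point, with nasal bleeding, nasal injury and the three airway maneuvers included) also reaches 18 to 21.

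**Step 2: independent tests, no true difference.**

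- Either direction: 1 − 0.95¹⁸ = 0.603; 1 − 0.95²¹ = 0.659.
- Favouring the WNJT: 1 − 0.975¹⁸ = 0.366; 1 − 0.975²¹ = 0.412.
- Expected false positives: 18 × 0.05 = 0.90 to 21 × 0.05 = 1.05 in total, half of them favouring the WNJT.

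**Step 3: correlated tests.** Simulation of equally correlated normal test statistics, 200,000 draws:

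| Correlation | Either direction, 18 / 21 tests | Favouring WNJT, 18 / 21 tests |
|---|---|---|
| 0 | 60% / 66% | 37% / 41% |
| 0.3 | 51% / 55% | 26% / 29% |
| 0.5 | 40% / 43% | 20% / 22% |

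At correlation 0.8, 21 tests give 23% and 11%.

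**Step 4: rare events.** By exact enumeration with 140 per group, the uncorrected chi-squared test has a type I error of 0.0055 at an event rate of 0.5%, 0.026 at 1% and 0.048 at 5%. Very rare events therefore add little. A patient-level simulation (140 per group, 18 tests, assumed event rates of 1% to 20%) allows for this. At patient-level correlation 0.5 it gives 52% in either direction and 28% favouring the WNJT. Over correlations 0 to 0.8 the ranges are 58% to 41% and 34% to 21%.

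**Step 5: satisfaction alone, favouring the WNJT.** 1 − 0.975³ = 0.073; 1 − 0.975⁶ = 0.141. These are for independent tests; positive correlation lowers them.

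**The case against.** The strongest objection is that multiplicity of secondary outcomes is commonly left to the analysis plan, which is not shown, and that a 5% threshold is conventional reporting language. That stands against any complaint about silence, and a plan not shown may hold a rule. It does not remove the point, because the article is not silent: it states an unrestricted rule and an aim that reaches the secondary outcomes. A later multiplicity rule would have to override that sentence.

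Four other objections stand, and they limit the point:

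- **Most of the count is safety.** Fifteen of the 18 to 21 comparisons are adverse events, which should not be multiplicity-adjusted in any case. For satisfaction alone the excess is much smaller (Step 5).
- **The Discussion hypothesis is narrow.** It does not mention satisfaction. Only the abstract's aim does.
- **The inputs are assumed.** The article does not say that every event is tested at every time point or that each rater scores twice, and it gives no rates for these events.
- **The choice of a key secondary outcome** has no basis in the article and belongs to the sponsor.

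A reader might also infer three stronger things that the article does not support:

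- *That a spurious WNJT benefit is likely.* No figure above for that direction reaches 50%. The larger percentages include errors against the device.
- *That a secondary result may rescue a null primary.* The article says no such thing. Its Discussion treats negative results as a reason for more research on preventing hypoxemia.
- *That there is no hierarchy at all.* Primary and secondary outcomes have separate headings, and the sample size rests on hypoxemia. The gap is within the secondary set.

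**Conclusion.** The point holds in a limited form, as an inexpensive improvement and not a flaw in the primary analysis. What needs correcting is the combination of an unrestricted threshold with an aim that makes complications and satisfaction part of the conclusion.

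The exposure to at least one false result favouring the WNJT spans roughly 11% (21 tests, correlation 0.8) to 41% (21 independent tests). The reference for one two-sided test is 2.5% in that direction, so the inflation is material even at the low end. If adverse events are regarded purely as safety reporting, what remains is the satisfaction claim, at no more than about 7% to 14%.

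All of this assumes no true difference on any secondary outcome. It also rests on my test count, assumed correlations and, in the patient-level simulation, assumed event rates.

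**What to change.** - In the analysis section, limit the P < 0.05 rule to the primary outcome.
- State there that secondary outcomes are supportive or exploratory and will be reported as between-group differences with 95% confidence intervals.
- State that harms, including nasal bleeding, are reported without multiplicity adjustment, so that no safety signal is suppressed.
- Reword the aim in the abstract's Discussion paragraph so that hypoxemia carries the conclusion and complications and satisfaction are described as supportive.
- Only if the sponsor wants a formal secondary claim: pre-specify a short sequence, with outcomes of the sponsor's choosing, tested only if the primary is significant and stopping at the first non-significant result.

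**Cost.** A few sentences, with no extra patients or data and no change to the stated sample size. The downside is that an isolated secondary P < 0.05 can no longer be reported as a demonstrated benefit. Trial status reports 20 of 308 participants recruited, and the interim analysis is set at half enrolment, so on those figures the change could be made before any planned comparison.

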### Handling of data

Study data are collected and managed by one statistician and checked by another statistician from the Clinical Research Institute of Beijing Friendship Hospital to promote data quality. An interim analysis will be performed by a data and safety monitoring board when half of the patients are enrolled. By this analysis, the data and safety monitoring board can advise on adjusting the study conduct, design, and others. Full access to the final trial dataset will be granted to the selected investigators only (YZ and [name]).

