### Randomization and blinding

According to a random number table generated by a computer, patients are randomly assigned to receive either the WNJT (group A) or the nasal prongs (group B). An online random list generation will be utilized to perform blocked randomization in a 1:1 ratio. Outcome assessment and statistical analysis will be performed by independent researchers who are from the Clinical Research Institute of Beijing Friendship Hospital and are blind to the group assignment.

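### The interim at half enrolment may change the design, but the only significance rule is the full 0.05, and the protocol does not say whether efficacy is examined there

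*Protocol article*

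**What the plan says.** Two sections of the protocol article bear on this point.

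- **Handling of data** commits the trial to one look: "An interim analysis will be performed by a data and safety monitoring board when half of the patients are enrolled". It then gives the look consequences: "the data and safety monitoring board can advise on adjusting the study conduct, design, and others". It names no outcome, comparison, test, stopping rule or interim significance level.
- **Sample size estimation and statistical analysis** sets the error rate for planning: "With an α = 0.05 and a power of 80%, we estimated that 140 patients per group would be required for our study". It does not state sidedness and does not mention an interim. The planning rates are 22% in group B and, with the WNJT, "the WNJT would achieve a reduction from 22% to 11% for the incidence of hypoxemia". With an allowance for dropout of about 10%, the total is 308. The decision rule is one general statement that a *P* "value < 0.05 is considered statistically significant", with no distinction between interim and final analysis.

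Allocation is by "blocked randomization in a 1:1 ratio" (Randomization and blinding). Trial status reports 20 patients recruited by 10 May 2018, so at that date the interim, at about 154 patients, still lay ahead.

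**The concern.** A look at accumulating data leaves the final 5% level intact only if it cannot feed the observed treatment difference back into the trial. The article gives the board a remit that includes the design and is otherwise open-ended. It leaves the only threshold at the full 0.05. Read together, the two sections allow two routes to a higher false-positive rate:

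1. The primary outcome is tested at the interim against the only stated threshold, and a significant result counts as success.
2. The rest of the trial is redesigned after the group difference has been seen, for example in its sample size, and the final test is still run at an unadjusted 0.05.

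At stake is whether a final *P* just below 0.05 on hypoxemia can be taken at face value. Readers will ask what was examined at half enrolment, and a rule written after that look carries little weight.

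**Working it through.** **Inputs from the article.** Alpha 0.05 (sidedness not given), power 80%, rates 22% and 11%, 1:1 allocation, 140 per group before dropout and 154 after, one interim at half enrolment, Chi-squared test for qualitative data.

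**Assumption.** Hypoxemia is observed during the gastroscopy itself, so half the patients carry about half the information: t = 0.5.

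**Step 1. Reproduce the plan's own figure.** Pooled-variance formula for two proportions, with mean rate (0.22 + 0.11)/2 = 0.165:

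n = [z_α √(2 × 0.165 × 0.835) + z_β √(0.22 × 0.78 + 0.11 × 0.89)]² / 0.11²

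- One-sided (z_α = 1.645, z_β = 0.842): n = 139.7, so 140. This matches.
- Two-sided (z_α = 1.960): n = 177.6, so 178.

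With dropout, 140 × 1.10 = 154 per group, or 308 in total, as printed. The figure therefore takes one analysis at the full 0.05. Of the variants tried (pooled, unpooled and arcsine; pooled also with continuity correction), only the one-sided pooled formula without correction gives 140. That is a separate matter, but it is why both sidedness readings are shown below.

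**Step 2. Type I error if both looks test the primary outcome at 0.05.** Under no effect, Z₁ (interim) and Z₂ (final) are standard normal with correlation √0.5 = 0.707. Then

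P(reject at either look) = P(|Z₁| > 1.96) + P(|Z₂| > 1.96) − P(both)

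= 0.0500 + 0.0500 − 0.0169 = **0.0831**.

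| Setting | Overall type I error |
|---|---|
| Two-sided 0.05 at both looks, t = 0.5 | 0.0831 |
| Same, t = 0.4 | 0.0863 |
| Same, t = 0.6 | 0.0796 |
| One-sided 0.05 at both looks, t = 0.5 | 0.0801 |
| Interim does not test efficacy and no change rests on the group difference | 0.05 |

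Simulated binomial data (1,000,000 replicates per setting, common rates of 11% to 22%, 140 or 154 per group, uncorrected Chi-squared test) gave 8.3% to 8.5% for the two-sided case.

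**Step 3. Boundaries that hold two-sided 5% at t = 0.5.**

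| Rule | Interim P | Final P |
|---|---|---|
| O'Brien-Fleming (z = 2.797, then 1.977) | 0.0052 | 0.0480 |
| Haybittle-Peto | 0.001 | 0.0498 |
| Pocock | 0.0294 | 0.0294 |

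Haybittle-Peto with the final test left at 0.05 gives 0.0502, so the correction is very small.

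**Step 4. Cost in power.** At 140 per group and 22% against 11%, two-sided power is 70.0% at 0.05. It is 69.4% for the final test alone at 0.0480, a loss of 0.6 percentage points before counting rejections at the interim. At Haybittle-Peto's final 0.0498 the change is smaller still.

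**Step 5. Redesign after seeing the difference.** The article states no adaptation rule, so the inflation by this route cannot be computed from it.

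**The case against.** A reader might infer that the trial as designed has a type I error of 8.3%, because it looks twice and has one threshold. The article does not support that. It does not say that the interim compares the groups on hypoxemia, that it is tested at 0.05, or that success may be claimed there. The board only advises. A safety review, or a check of the pooled hypoxemia rate, fits the wording equally well, and in either case the final test keeps its 5% level. For the same reason, it would go too far to say that the board will see unblinded effect data or that the trial can claim success twice. This part of the objection stands, and it makes the 8.3% conditional.

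It can also be said that boundaries usually sit in an analysis plan or board charter, neither of which is shown, and that an article may leave them there. That is fair, and a missing boundary alone would be no finding. But the article itself prints a remit that extends to the design, together with a single full-alpha threshold. If a charter sets a reduced final level, the printed threshold disagrees with it. If none does, nothing shown rules out an effect-driven change followed by an unadjusted test.

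Finally, the article says that outcome assessment and statistical analysis are done by researchers blind to group assignment. This does not settle the matter. The interim is assigned to the board, and a comparison of two coded groups still shows the size of the difference.

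**Conclusion.** The point holds in conditional form and is of moderate severity. The article plans an interim with consequences for the design, uses the full 0.05 as its only threshold, and does not confine the interim to safety or blinded data.

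- If hypoxemia is tested at 0.05 at the interim and success may be claimed there, overall type I error is about 8.3% two-sided, or about 8.0% if both looks are one-sided at 0.05. This assumes a look at half the information; between 40% and 60% of the information, the two-sided figure runs from 8.6% to 8.0%.
- If design changes follow from the observed group difference, the error may also rise, by an amount the document does not fix.
- If the interim is limited to safety or pooled blinded data, the final 5% level holds and nothing needs adjusting.

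The article does not say which of these applies.

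**What to change.** Before the interim takes place, add one of two statements to the protocol and repeat it in the board's charter:

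1. **No efficacy look.** The interim does not test efficacy, and any design change rests only on safety or on the pooled, blinded hypoxemia rate. The final test stays at 0.05.
2. **Efficacy look with a boundary.** Name the outcome and the test, and fix the levels, for example Haybittle-Peto at two-sided 0.001 then 0.0498, or O'Brien-Fleming at 0.0052 then 0.0480. Replace the general 0.05 threshold with the reduced level for the final primary test. Any design change based on the group difference would need its own pre-specified method.

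These levels are two-sided, so the sidedness of the 0.05 should be stated at the same time; a one-sided 0.05 would need its own boundary.

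The first option is simpler and leaves the analysis unchanged. Either costs one or two sentences. The second also costs at most about 0.6 percentage points of power at the planned size, and needs no more patients in practice.

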### Study dropouts

Investigators have the right to terminate participation of any individuals at any time if the investigator deems it in the participant’s best interest. Furthermore, the individual has the right to withdraw the consent to participate in the study at any time for any reason without any consequences for further medical treatment. The study discontinuation will be documented.

## Discussion

Hypoxemia caused by transient respiratory inhibition and airway obstruction is common during gastroscopy with intravenous anesthesia or sedation, especially in obese patients due to altered anatomy of the airway, reduced functional residual volume of the lungs, and decreased compliance of the chest wall [12]. Although respiratory depression may be transient and spontaneously recover with or without intervention, it can result in a risk of interrupting or stopping the gastroscopic procedure and even lethal hypoxemia requiring emergent management. The nasopharyngeal airway can prevent airway obstruction caused by the falling tongue and reduce air flow resistance, thus facilitating spontaneous breathing and decreasing the occurrence of hypoxemia during gastroscopy with intravenous anesthesia or sedation [26].

This RCT is designed to test the hypothesis that the WNJT, a new kind of nasopharyngeal airway, can reduce the incidence of hypoxemia and related adverse events. We believe that the findings of this study will have significant clinical implications; even negative results are obtained. This would mean that more studies are needed to explore a safe and effective method to prevent hypoxemia during gastroscopy with intravenous anesthesia or sedation in obese patients. This is one of the main strengths of present study.

There are some issues in our study design that need to be noted. First, this is a single-blinded protocol, as the investigator knows whether nasal prongs or the WNJT are used. This may bias the findings of this study. Second, as the nasal soft tissue is easily damaged [27], the WNJT may lead to discomfort and even nasal bleeding or injury, as reported in a previous study [15]. Furthermore, the nasal bleeding or injury may only occur in the group A. Although the nasal bleeding and injury associated with nasopharyngeal airway are often slight, care should be taken to avoid this; essential management is required if they occur, especially for patients with nasal stenosis [28].

In summary, this single-center, prospective RCT will compare the efficacy and safety of using the WNJT and nasal prongs for supplemental oxygen during gastroscopy with intravenous propofol anesthesia in obese patients. The result of the trial will provide the evidence for anesthesiologists to make a decision regarding the choice of supplemental oxygen methods in this condition.

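### Nasal bleeding, a harm the protocol says may occur only with the WNJT, is left to a blanket chi-squared test that says little at low counts; a group A rate with an exact interval would serve better

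*Protocol article*

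**What the plan says.** The Secondary outcomes section of the protocol article names the harm: "The secondary outcomes are the adverse events during the gastroscopy, nasal bleeding or injury, complications", followed by satisfaction. Bleeding is graded 0 to 3 under Data about the procedure, and is collected again at recovery of consciousness and 30 minutes later under Data after the procedure.

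The analysis section has one rule for all categorical outcomes: "Qualitative data will be expressed as n (%) and compared using a Chi-squared test". The threshold is a P "value < 0.05 is considered statistically significant". It gives no separate rule for bleeding and names neither a continuity correction nor an alternative for small counts.

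The Discussion, listing issues in the study design, states: "Furthermore, the nasal bleeding or injury may only occur in the group A". Other sections share that premise. The Background calls WNJT placement invasive, with a possible risk of nasal injury and bleeding, and the Interventions section describes a response to bleeding for group A only.

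**The concern.** The stated test does not suit the protocol's own premise. If bleeding arises essentially in one arm, whether the two rates are equal is not the useful question. A clinician choosing between the devices needs to know how often the WNJT causes bleeding and how high that rate could plausibly be. A chi-squared P value answers neither. With no bleeds in group B it reduces to asking whether the group A count passed a fixed small number, and at such counts its large-sample approximation is poor.

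The article says the trial will compare efficacy and safety and inform the choice of oxygen method. A line showing a few bleeds against none with P above 0.05 would be a weak basis for the safety half of that comparison.

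**Working it through.** **Inputs from the protocol article.** 140 evaluable and 154 enrolled patients per group; chi-squared test; threshold 0.05. The protocol gives no bleeding rate for either group.

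**Assumptions made here.** Bleeding is reduced to any versus none. Group B has 0 bleeds, unless stated otherwise. The true group A rate is varied from 1% to 10%.

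**1. The plan's own figure.** The only sample size stated is for hypoxemia, 22% versus 11%: "we estimated that 140 patients per group would be required for our study". With pooled variance and no continuity correction,

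n = [z(α)·√(2·0.165·0.835) + 0.8416·√(0.22·0.78 + 0.11·0.89)]² / 0.11².

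- One-sided α = 0.05: (1.6449·0.5249 + 0.8416·0.5191)² / 0.0121 = 139.7, so 140.
- Two-sided α = 0.05: 178.
- 154 = 140 × 1.10.

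The 140 therefore reproduces with a one-sided α. That is a separate matter; here 140 and 154 serve only as group sizes.

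**2. How many group A bleeds give significance against 0 in group B?** For k versus 0 with n per group:

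- Pearson: χ² = 2nk / (2n − k).
- Yates: χ² = 2n(k − 1)² / [k(2n − k)].
- Fisher, two-sided: P = 2·C(n,k) / C(2n,k).

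At n = 140, Pearson for k = 3 is 840/277 = 3.03, P = 0.082; for k = 4 it is 1120/276 = 4.06, P = 0.044. At n = 154 the P values are the same to three decimals.

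| Bleeds A vs B (n = 140) | Pearson | Yates | Fisher |
|---|---|---|---|
| 4 vs 0 | 0.044 | 0.13 | 0.12 |
| 5 vs 0 | 0.024 | 0.071 | 0.060 |
| 6 vs 0 | 0.013 | 0.039 | 0.030 |

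Pearson needs 4 bleeds; Yates and Fisher need 6. With 4 or 5 bleeds the verdict depends on a choice the article does not state. The expected count per arm is k/2, which is below 5 for any total under 10 bleeds.

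**3. Chance of a non-significant result.** This is the binomial probability P(X ≤ 3) for Pearson and P(X ≤ 5) for Yates or Fisher. For n = 140 and a 2% rate, P(X ≤ 3) = 0.0591 + 0.1689 + 0.2395 + 0.2249 = 0.692.

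| Assumed true group A rate | Pearson, n = 154 / 140 | Yates or Fisher, n = 154 / 140 |
|---|---|---|
| 1% | 93.0% / 94.7% | 99.5% / 99.7% |
| 2% | 62.9% / 69.2% | 91.0% / 93.7% |
| 3% | 31.9% / 39.2% | 68.3% / 75.5% |
| 5% | 4.8% / 7.7% | 21.3% / 29.4% |
| 10% | under 0.1% | 0.1% / 0.4% |

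A non-zero group B rate makes detection harder. At 2% versus 0.5%, Pearson is non-significant in 81.5% / 83.9% of trials.

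**4. What an exact interval would show.** Clopper–Pearson 95% limits for group A:

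- 0/154: 0 to 2.4% (upper limit 1 − 0.025^(1/154)). 0/140: 0 to 2.6%.
- 3/154: 0.4% to 5.6%. 3/140: 0.4% to 6.1%.

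With 3 bleeds against none, the planned table would read P = 0.08, while the data would be compatible with a bleeding rate above 5%.

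**The case against.** The strongest reply is that this asks for detail that a condensed article may leave to a fuller document. Interval methods and small-count handling for one secondary harm often sit in an analysis plan, which is not shown. Low power for a rare harm is also ordinary in a trial sized on its primary outcome. Both points limit the severity. They do not remove the point, because the article states a test for this outcome and that test fits poorly with its own remark about group A.

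Several stronger readings are tempting and are not supported:

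- **That the trial will call the device safe when P exceeds 0.05.** No sentence says so. The sentence that sets the test also requires counts and percentages, so the group A numerator will be published and a reader could derive the limit.
- **That the trial will miss a WNJT bleeding excess in 63–69% of cases.** That range belongs to a 2% rate, which appears nowhere in the protocol. At 5% or more the uncorrected test usually detects the excess. The range also depends on an uncorrected test, a collapsed scale and no bleeds in group B.
- **That every group A bleed is caused by the device.** The article says bleeding *may* occur only in group A, and the post-procedure collection of bleeding is not limited to one group.

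The article also openly lists the asymmetry as a design issue and describes such bleeding as often slight.

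**Conclusion.** The point holds in a limited form. The one stated inference for nasal bleeding or injury is poorly suited to a harm the protocol thinks may arise in one arm only, and it is unreliable at the counts where it would matter. The article supplies percentages but no stated measure of how high the device's bleeding rate could be.

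The size depends on an unknown rate: non-significance with the uncorrected test is near-certain at 1% and uncommon at 5%, and more frequent throughout with Yates or Fisher. These figures assume no bleeds in group B and an any-versus-none outcome. A reader should not infer that the protocol plans to equate non-significance with safety. This is a cheap improvement of low to moderate severity.

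**What to change.** Add to the section on sample size and statistical analysis, in wording such as:

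> The proportion of group A patients with nasal bleeding (any grade, and grade 2 or higher) and, separately, with nasal injury will be reported with exact (Clopper–Pearson) 95% confidence intervals, alongside the corresponding group B counts. Statements about nasal safety will rest on these intervals and not on the absence of statistical significance. If a between-group P value is also shown, Fisher's exact test will be used.

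The grade cut applies to bleeding only, because the 0–3 scale does not grade injury. A P value need not be banned. The interval is descriptive: the sentence sets no acceptable limit and so adds no pass-or-fail rule.

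The cost is one sentence and a few intervals. Bleeding is already graded and recorded, and nasal injury is already a named outcome. No extra patients are needed. The downside is that the published safety statement may look less favourable than a report of no significant difference.
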